### Safety

The investigators will inform the patients, the study monitoring board, and the ethics committee if it becomes evident that the disadvantages of participation may be significantly greater than was foreseen in the research proposal. The study will be suspended pending further review by the study monitoring board, except insofar as suspension would jeopardize the patients’ health. The investigators will take care that all patients are kept informed.

Adverse events will be assessed and categorized according to the National Cancer Institute Common Terminology Criteria for Adverse Events (CTCAE) version 4 in grade 1 to 5 (http://ctep.cancer.gov/protocolDevelopment/electronic_applications/ctc.htm). All adverse events will be followed until they have abated, or until a stable situation has been reached. Depending on the event, follow-up may require additional tests or medical procedures as indicated, and/or referral to the general physician or a medical specialist.

In the case of withdrawal of consent to participate in the study, all possible efforts will be made to convince the patient to continue to have safety follow-up evaluations.

In the event one of the following situations arises among treated patients during the conduct of the study, the study will be temporarily suspended and a comprehensive safety review conducted evaluating if the study has to be terminated prematurely:Any death secondary to rapid unexpected progression of an underlying medical condition.Severe clinical or neurological deterioration in more than one subject.Any other serious adverse event determined by the study monitoring board to be a reason to suspend the study.

### Study outcome measures

Primary: Success of intravesical treatment, defined as normalization of urine culture (no evidence of bacteria, i.e. <10^4^ colony forming units/mL) after 7 days of bacteriophage, placebo, or antibiotic treatment.

Secondary: Adverse events, in categorization according to the National Cancer Institute Common Terminology Criteria for Adverse Events (CTCAE) version 4 in grade 1 to 5 (http://ctep.cancer.gov/protocolDevelopment/electronic_applications/ctc.htm) during treatment phase.

Tertiary: a) Changes in bladder and pain diary assessment of number of voids, number of leakages, post void residual, pain assessment using a visual analog scale (0 (no pain) to 10 (strongest possible pain)), b) IPSS items at baseline versus day 7 under intravesical bacteriophage, placebo, or antibiotic treatment.

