## Methods and design

### Study design

This study is a randomized, placebo-controlled, double-blind trial investigating bacteriophages in UTI treatment. The study is conducted at the Tzulukidze National Center of Urology (TNCU), Tbilisi, Georgia. Phage preparations (i.e. Pyo bacteriophage solution: commercially available and registered in Georgia) and continuous adaption cycles during the course of the study, to enhance the treatment effect, are done at the Eliava Institute of Bacteriophages, Microbiology, and Virology in Tbilisi (EIBMV), Georgia.

Figure 1 gives an overview of the procedures. Patients planned for transurethral resection of the prostate are screened for UTIs at the TNCU. Urine cultures including antibiotic sensitivity testing are performed in a duplicate manner. If eligible microorganisms which would potentially match with the type of bacteriophage present in Pyo bacteriophage (5 components: Enterococcus spp., *Escherichia coli*, Proteus mirabilis, Pseudomonas aeruginosa, Staphylococcus spp., and Streptococcus spp.) are detected, urine cultures are then sent for bacteriophage sensitivity testing to the EIBMV (Fig. 2) [12]. In case of a positive in-vitro sensitivity testing, concluded within 24 h after receipt of the urine culture, patients will be asked for study participation. After written informed consent, patients are randomized in a double-blind fashion to the study treatment arms in a 1:1:1 ratio to receive either: a) Pyo bacteriophage solution, b) placebo (sterile bacteriology media with identical color as treatment arm a), or c) antibiotic treatment according to the antibiotic sensitivity pattern, respectively. Treatment arms a and b will be double-blind but treatment arm c, i.e. the control arm representing common clinical practice, is open label. All treatments are intended for 7 days starting at the day of surgery (arm c) or one day thereafter (arm a and b). Prior and at the end of treatment (i.e. after 7 days) or at withdrawal / drop out, urinalysis, urine culture, bladder and pain diary [18] and an International Prostate Symptom Score (IPSS) questionnaire [19] will be taken. Patients with persistent bacteriuria will undergo antibiotic treatment according to antibiotic sensitivity.

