### Determination of sample size

We are planning a study of independent cases and controls with 1 control per case. Superiority of bacteriophage versus placebo treatment: We assume the success rate among controls to be 0.2. If the true success rate for experimental subjects is 0.6, we will need to study 27 experimental and 27 control subjects to be able to reject the null hypothesis that the success rates for experimental and control subjects are equal with probability (power) 0.8. The type I error probability associated with this test of this null hypothesis is 0.05.

Non-inferiority of bacteriophage versus antibiotic treatment: We assume the success rate among subjects receiving bacteriophage treatment to be 0.6 and we accept a non-inferiority margin of 0.35. If the true success rate for experimental subjects is 0.95, we will need to study 27 experimental subjects and 27 control subjects to be able to remain within the non-inferiority margin with a probability (power) 0.8. The type I error probability associated with this test of this alternative hypothesis is 0.05. We will use a continuity-corrected chi-squared statistic or Fisher’s exact test to evaluate these hypotheses.

Thus, we will include 27 patients per treatment group, i.e. 81 patients in total. Withdrawn patients will be replaced.

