### Investigations

The patients planned for transurethral resection of the prostate with a positive urine culture (≥10^4^ colony forming units/mL) of predefined uropathogens sensitive to Pyo bacteriophage (i.e. Enterococcus spp., *Escherichia coli*, Proteus mirabilis, Pseudomonas aeruginosa, Staphylococcus spp., and Streptococcus spp.) and fulfilling the study inclusion criteria will be included into the study after providing written informed consent. The patients will be assessed using bladder and pain diary [18] and an IPSS questionnaire [19]. The Fig. 1 gives an overview of the procedures that patients will undergo during the study.

After inclusion, patients will be randomized in a double-blind fashion to the study treatment arms in a 1:1:1 ratio. Patients of all study arms will undergo monopolar transurethral resection of the prostate and insertion of a suprapubic catheter if not already present. Study arm a) will receive bacteriophage solution (Pyo bacteriophage) and study arm b) placebo solution (sterile bacteriology media). Either solution will consist of 20 mL and will have an identical appearance for both the bacteriophage and the placebo, respectively. An investigator not involved in the assessment of the clinical outcome will deliver the solution and teach the patient / health care provider how to instill the solution into the bladder. The solution will be instilled using the suprapubic catheter, 2 times per 24 h (i.e. 8.00, 20.00) for 7 days, starting the first day after surgery. The patients will be asked to retain the solution in the bladder for approximately 30–60 min. No antibiotic prophylaxes will be given to the study treatment arms a and b.

Study arm c) will receive an antibiotic treatment according to the antibiotic sensitivity pattern and common clinical practice.

At the end of treatment (i.e. after 7 days) or at withdrawal / drop out, urinalysis, urine culture, bladder and pain diary [18] and an IPSS questionnaire [19] will be taken. Patients with persistent UTIs will undergo antibiotic treatment according to antibiotic sensitivity for 7 days.

Drop out criteria for patients in the study arm a and b are fever >38 °C, CRP >100 mg/L, other clinical signs or symptoms for a systemic infection or withdraw from the patients. These patients will undergo antibiotic treatment according to antibiotic sensitivity.

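### The adverse-event outcome is limited to an undefined treatment phase; with staggered treatment starts, a literal reading counts the day of surgery only in the antibiotic arm

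*Protocol article*

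**What the plan says.** All references are to the Protocol article.

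- **Outcome window (Study outcome measures).** The secondary outcome is adverse events graded by CTCAE version 4, and the sentence ends "http://ctep.cancer.gov/protocolDevelopment/electronic_applications/ctc.htm) during treatment phase". The article does not say when that phase begins or ends.
- **Treatment start (Study design).** "All treatments are intended for 7 days starting at the day of surgery (arm c) or one day thereafter (arm a and b". The Investigations section agrees for arms a and b: instillations run "for 7 days, starting the first day after surgery".
- **Surgery (Investigations).** Randomisation is described first; then "Patients of all study arms will undergo monopolar transurethral resection of the prostate".
- **Antibiotic cover (Investigations).** "No antibiotic prophylaxes will be given to the study treatment arms a and b".
- **General safety text (Safety).** Events are assessed and graded, and "All adverse events will be followed until they have abated, or until a stable situation has been reached". No start of collection is given, and the outcome window is not widened.

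**The concern.** A randomised safety comparison needs the same observation period in every arm, counted from a point that does not depend on allocation. Here the only stated period is tied to treatment, and treatment starts on different days by arm.

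The day that falls differently is the day of the resection. Every patient enters with a positive urine culture and symptoms. Arms a and b are operated on without antibiotic prophylaxis. Operative events, and any infectious event that appears the same day, occur after randomisation and so belong in the comparison. If they are counted in arm c and not in arms a and b, the two strategies are compared over different periods. The Background section names safety as one of the trial's two aims, and Study design describes arm c as the control that represents common practice. The affected contrast is therefore one that readers will look at.

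**Working it through.** The plan gives no figure on this point to reproduce. The check is one of timing, followed by an illustration of size.

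**Step 1: days counted.** Let day 0 be the day of surgery. Each arm has 7 days of treatment; the start is day 0 in arm c and day 1 in arms a and b (Study design; Investigations).

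- Arm c: 0, 1, 2, 3, 4, 5, 6
- Arms a and b: 1, 2, 3, 4, 5, 6, 7
- In c only: day 0. In a and b only: day 7.

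The windows are equally long but shifted by one day. Arms a and b share the same window, so their blinded comparison is balanced, although neither counts the day of surgery.

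**Step 2: what the shift does.** Suppose the true risk is the same in all three arms, with probability p0 of an event on day 0 and p on each later day, independently between days. The proportion with at least one counted event is:

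- arm c: 1 − (1 − p0)(1 − p)^6
- arms a and b: 1 − (1 − p)^7
- difference, c minus a or b: (1 − p)^6 × (p0 − p)

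The difference is zero if p0 = p, favours a and b if p0 > p, and favours c if p0 < p. The day-7 offset is therefore included.

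**Step 3: illustration.** The article gives no adverse-event rates or onset times, so p0 and p are assumptions. The 27 patients per arm come from Determination of sample size ("we will include 27 patients per treatment group, i.e. 81 patients in total"). Example with p0 = 0.20 and p = 0.01: 0.99^6 = 0.941; 0.941 × 0.19 = 0.179; 27 × 0.179 = 4.8 patients.

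| p0 (day 0) | p (other days) | Arm c | Arms a, b | Difference | Patients of 27 |
|---|---|---|---|---|---|
| 0.05 | 0.01 | 0.106 | 0.068 | 0.038 | 1.0 |
| 0.05 | 0.03 | 0.209 | 0.192 | 0.017 | 0.4 |
| 0.10 | 0.01 | 0.153 | 0.068 | 0.085 | 2.3 |
| 0.10 | 0.03 | 0.250 | 0.192 | 0.058 | 1.6 |
| 0.20 | 0.01 | 0.247 | 0.068 | 0.179 | 4.8 |
| 0.20 | 0.03 | 0.334 | 0.192 | 0.142 | 3.8 |
| 0.30 | 0.01 | 0.341 | 0.068 | 0.273 | 7.4 |
| 0.30 | 0.03 | 0.417 | 0.192 | 0.225 | 6.1 |

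The true risks are identical by construction, so each difference comes from the window alone. The table also assumes that an event is counted by its day of onset. If an event that begins on day 0 and is still present on day 1 is counted in arms a and b, the gap shrinks.

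**The case against.** The strongest reply is that the key term is undefined. It could mean a trial-level period between the baseline and end-of-treatment assessments, which would include surgery. The procedures figure is not available, and a full protocol may fix the dates. This stands as a limit: the article does not state that the day of surgery is excluded, only that a literal reading excludes it. It does not remove the point. The article gives explicit arm-specific starts and offers nothing in support of the wider reading. The point rests on the window as stated, not on detail left out.

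A second reply is that the Safety section already requires adverse events to be assessed, graded and followed. This also stands in part. Surgery-day events may well be recorded, so the issue is which events enter the stated outcome, not lost data. It is also true that the formal hypotheses and the sample size concern efficacy only.

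Two stronger readings are tempting, and the article does not support them:

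- **That the window closes when a patient in arm a or b drops out for systemic infection, so later worsening is lost.** No section says so. The Safety section points the other way, since all events are followed until they abate or are stable, and safety follow-up is sought even after consent is withdrawn. An infection that triggers drop-out after dosing has begun has already arisen within the treatment phase.
- **That the safety comparison is certainly biased in favour of bacteriophage and placebo.** Day 7 counts only in arms a and b. If events were spread evenly over the days, the shift would make no net difference.

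**Conclusion.** The point holds in a limited form. Read literally, the adverse-event outcome covers days 0-6 in arm c and days 1-7 in arms a and b, so the operating day is counted only in the arm that receives antibiotics. The comparison of a or b with c is not like for like. The comparison of a with b has equal windows, but both arms omit surgery-day events.

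The direction depends on onset timing, which the article does not give. More events on the day of surgery than on day 7 is plausible and would make arms a and b look safer than they are. Under the assumed risks above, the artefact ranges from less than one patient to about seven patients of 27. That range shows what the wording could do; it does not estimate this trial. The primary outcome, a urine culture result, is not affected.

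**What to change.** Replace the reference to the treatment phase with one window for all three arms: adverse events from randomisation, or from the start of surgery, to the same day counted from surgery, regardless of whether study treatment has started or stopped. Days 0 to 7 after surgery is the shortest common window that contains the 7-day course of every arm.

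The cost is one sentence. It changes which events are counted and leaves every treatment schedule as it is. The events are already to be assessed and graded under the Safety section. The small downside is that a few more events will be reported in arms a and b from the day of surgery and, if the window ends on day 7, any day-7 events in arm c as well.

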**Methods and design:**

This study is the first randomized, placebo-controlled, double-blind trial investigating bacteriophages in UTI treatment. Patients planned for transurethral resection of the prostate are screened for UTIs and enrolled if in urine culture eligible microorganisms ≥10^4^ colony forming units/mL are found. Patients are randomized in a double-blind fashion to the 3 study treatment arms in a 1:1:1 ratio to receive either: a) bacteriophage (i.e. commercially available Pyo bacteriophage) solution, b) placebo solution, or c) antibiotic treatment according to the antibiotic sensitivity pattern. All treatments are intended for 7 days. No antibiotic prophylaxes will be given to the double-blinded treatment arms a) and b). As common practice, the Pyo bacteriophage cocktail is subjected to periodic adaptation cycles during the study. Urinalysis, urine culture, bladder and pain diary, and IPSS questionnaire will be completed prior to and at the end of treatment (i.e. after 7 days) or at withdrawal/drop out from the study. Patients with persistent UTIs will undergo antibiotic treatment according to antibiotic sensitivity pattern.

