#### Univariate analysis

T-tests will be used to compare means between groups and chi-squared tests to compare dichotomous variables.

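### Interval-scaled tertiary outcomes would be better compared at day 7 with their own baseline always in the model: surgery lies between the two readings, and a t-test on change is valid but less precise

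*Protocol article*

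**What the plan says.** All references are to the protocol article.

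- **Outcomes (Study outcome measures, Tertiary).** Part (a) is "Changes in bladder and pain diary assessment of number of voids, number of leakages, post void residual, pain assessment using a visual analog scale". Part (b) is "b) IPSS items at baseline versus day 7 under intravesical bacteriophage, placebo, or antibiotic treatment".
- **Timing of readings.** The abstract's Methods and design paragraph says: "Urinalysis, urine culture, bladder and pain diary, and IPSS questionnaire will be completed prior to and at the end of treatment". Investigations describes the assessment at inclusion ("The patients will be assessed using bladder and pain diary [18] and an IPSS questionnaire [19"), before it comes to randomisation and surgery.
- **Surgery (Investigations).** "Patients of all study arms will undergo monopolar transurethral resection of the prostate and insertion of a suprapubic catheter if not already present".
- **Start of treatment (Study design).** Treatment runs for 7 days, "starting at the day of surgery (arm c) or one day thereafter (arm a and b").
- **Analysis.** Univariate analysis says: "T-tests will be used to compare means between groups". Multivariate analysis then provides linear models for interval-scaled outcomes, with the stated purpose of adjusting for baseline parameters that are unequally distributed. It names no covariates. Neither section says whether the t-test takes the change or the day-7 value, or whether the adjusted or unadjusted result leads.

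**The concern.** Voiding frequency, residual volume, pain and IPSS are quantities that a prostate resection and a new suprapubic catheter can be expected to move. If baseline is pre-operative, a before-after change within an arm contains the effect of the operation as well as that of the allocated treatment. Describing the outcome as baseline versus day 7 under each treatment invites a reader to credit that change to the treatment.

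For the between-arm comparison the issue is efficiency. A change score subtracts the whole baseline value, whatever its relation to the day-7 value. If surgery weakens that relation, the subtraction adds noise. A linear model estimates how much of the baseline to remove. Tying the model to baseline imbalance also leaves open which analysis leads, and that choice could be made after the data are seen. With 27 patients per arm, precision is worth keeping when it costs nothing to collect.

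**Working it through.** **The article's own figure.** No sample size, standard deviation, correlation or power is given for the tertiary outcomes. The only figure is 27 per arm, from the primary endpoint (Determination of sample size: 0.2 versus 0.6, power 0.8, alpha 0.05, taken as two-sided).

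- Uncorrected: n = [1.960·√(2·0.4·0.6) + 0.842·√(0.2·0.8 + 0.6·0.4)]² / 0.4² = (1.358 + 0.532)² / 0.16 = 22.3, so 23.
- Continuity-corrected: (22.33/4)·[1 + √(1 + 4/(22.33·0.4))]² = 27.1, so 28 when rounded up.

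The stated 27 is reproduced to within one patient, and 27 per arm is used below.

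**Assumptions not in the article.** rho is the correlation between the baseline and day-7 values. k is the baseline SD divided by the day-7 SD. The day-7 SD is set to 1.

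**Variance per patient.**

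- Change score: 1 + k² − 2·rho·k
- Day-7 value alone: 1
- Day-7 value adjusted for baseline: 1 − rho²

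Change score minus adjusted is (k − rho)², which is never negative. Apart from the one degree of freedom, the change score is therefore never more precise, and it is equally precise only when k = rho.

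**Equal SDs (k = 1).** The change-score variance is 2(1 − rho), so adjusted divided by change is (1 − rho²)/[2(1 − rho)] = (1 + rho)/2. The change score is noisier than the day-7 value alone when 2(1 − rho) > 1, that is, when rho < 0.5.

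**Power.** Take the effect that gives the adjusted analysis 80% power with 27 per arm, two-sided 0.05, normal approximation. The change-score power is then Φ(2.802·√((1 + rho)/2) − 1.960). At rho 0.3, for example, this is Φ(2.259 − 1.960) = Φ(0.299) = 62%.

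| rho | Variance, adjusted / change | Power, change score | Power, day 7 alone | Power, adjusted |
|---|---|---|---|---|
| 0.1 | 0.55 | 55% | 80% | 80% |
| 0.3 | 0.65 | 62% | 76% | 80% |
| 0.5 | 0.75 | 68% | 68% | 80% |
| 0.7 | 0.85 | 73% | 52% | 80% |
| 0.9 | 0.95 | 78% | 23% | 80% |

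In patients per arm, 27·(1 − 0.65) is about 9 at rho 0.3, and 27·(1 − 0.95) is about 1 at rho 0.9.

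**Unequal SDs.** The change-score power, again where the adjusted analysis has 80%:

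| k | rho 0.2 | rho 0.5 | rho 0.8 |
|---|---|---|---|
| 0.5 | 76% | 80% | 71% |
| 1.0 | 58% | 68% | 76% |
| 1.5 | 39% | 45% | 45% |

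The loss disappears at k = rho = 0.5, as the formula requires, and grows when baseline is more variable than day 7.

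**The case against.** Four counter-arguments deserve weight.

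1. **No within-arm inference is planned.** A reader might infer that each arm will be credited with a treatment change that is really the operation. The article does not support this. The t-test is between groups, and no paired or before-after test is stated. The outcome wording leaves room for such a reading but does not set that contrast. This objection stands.

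2. **Surgery is common to all arms.** A reader might infer that it biases the treatment comparison. It does not: the arms are randomised and all have the resection, so its shared effect cancels. One reservation concerns the antibiotic arm. Its treatment starts a day earlier relative to surgery, so its day-7 reading may fall a day sooner after the operation. That is a matter of timing and is not cured by the choice between change score and adjustment.

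3. **Use of change scores is inferred.** Part (a) says changes and part (b) says baseline versus day 7, but the t-test is not tied to either. If day-7 values are tested, the change-score losses do not apply. There is then a different loss from ignoring baseline, and it is larger at high rho.

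4. **Baseline adjustment is already present.** Linear models are provided, and the diary and IPSS are among the variables listed under Study population and recruitment. It would be wrong to say that baseline is not adjusted for. The phrase about unequal distribution can also be read as the purpose of the models and not as a condition for using them. A covariate list is normally left to the analysis plan, so its absence is no fault. What remains is that the stated rationale is imbalance, and nothing says which of the two results leads.

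The pre-operative baseline is also a natural reading and not an explicit statement. The abstract says only that readings precede treatment, and in the two blinded arms treatment starts the day after surgery.

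**Conclusion.** The point holds as a minor, cost-free improvement and not as an error that invalidates an analysis. An unadjusted between-arm t-test on change is valid here. If that is what is meant, it is less precise than a baseline-adjusted day-7 comparison in all but special cases. With equal SDs the variance ratio is 0.55 to 0.95 for rho 0.1 to 0.9, which is about 25 points down to 2 points of power lost from 80%.

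The size rests on a correlation and SDs that the article does not give, and on the inference that change scores are tested. That surgery weakens the correlation is plausible but not shown. The outcomes are tertiary, no power is claimed for them, and the primary analysis is untouched. Within-arm changes need a caution in presentation, because they include the effect of surgery.

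**What to change.** - **Study outcome measures (Tertiary):** define each interval-scaled outcome as the between-arm difference in the day-7 value. State that baseline is the pre-operative reading, if that is what is intended.
- **Univariate and Multivariate analysis:** analyse each of these outcomes with a linear model that always includes that outcome's own baseline value, whether or not the arms differ at baseline. Name this as the leading result. An unadjusted t-test, if kept, is supportive.
- **Presentation:** report within-arm before-after changes descriptively only, with a note that they include the effect of the resection and catheter.

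The cost is one degree of freedom per model and a few lines of wording. No new data are needed, since the article already schedules both readings.
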